### 3.2 PHASE II OBJECTIVES & ENDPOINTS

| Objectives                                                                                                                                                                                                                                                                                                                                                 | Endpoints                                                                                                                                                                                                                                                                                                                                                                                                                                                                                                                                                                                                                                                                                                                                                                                      |
|------------------------------------------------------------------------------------------------------------------------------------------------------------------------------------------------------------------------------------------------------------------------------------------------------------------------------------------------------------|------------------------------------------------------------------------------------------------------------------------------------------------------------------------------------------------------------------------------------------------------------------------------------------------------------------------------------------------------------------------------------------------------------------------------------------------------------------------------------------------------------------------------------------------------------------------------------------------------------------------------------------------------------------------------------------------------------------------------------------------------------------------------------------------|
| Primary                                                                                                                                                                                                                                                                                                                                             |                                                                                                                                                                                                                                                                                                                                                                                                                                                                                                                                                                                                                                                                                                                                                                                                |
| To investigate the efficacy of IV Favipiravir compared with placebo to reduce the SARS-CoV-2 viral load                                                                                                                                                                                                                                                    | 
 
• Change from baseline to Day 3 in SARS-CoV-2 viral load
 
                                                                                                                                                                                                                                                                                                                                                                                                                                                                                                                                                                                                                                                                                     |
| Secondary                                                                                                                                                                                                                                                                                                                                           |                                                                                                                                                                                                                                                                                                                                                                                                                                                                                                                                                                                                                                                                                                                                                                                                |
| Safety objective: To determine the safety and tolerability of IV Favipiravir                                                                                                                                                                                                                                                                        | 
 
• AEs, SAEs, targeted physical findings, vital signs and laboratory parameters
 
                                                                                                                                                                                                                                                                                                                                                                                                                                                                                                                                                                                                                                                               |
| Pharmacokinetic objective: To characterise the plasma PK of IV Favipiravir                                                                                                                                                                                                                                                                          | 
 
• PK parameters of IV Favipiravir up to Day 8
 
                                                                                                                                                                                                                                                                                                                                                                                                                                                                                                                                                                                                                                                                                                |
| Virological objective: To investigate the efficacy of IV Favipiravir on SARS-CoV-2 viral load                                                                                                                                                                                                                                                       | 
 
• Change from baseline over time, up to Day 29, in viral load
 
• Time to negative viral titres (Day 1-29)
 
                                                                                                                                                                                                                                                                                                                                                                                                                                                                                                                                                                                                                            |
| 
Clinical objectives:
 
To compare the effect of IV Favipiravir versus placebo on overall mortality, time to discharge, duration of oxygen use (and oxygen free days) and incidence and duration of new mechanical ventilation use
 
To evaluate time to, and proportion of, clinical improvement (WHO clinical progression scale).
 | 
 
• Mortality at Days 8, 15 and 29 (Time to death from randomisation)
 
• Proportion of patient discharged by days 8, 15 and 29 (Time to discharge from randomisation)
 
• Duration (days 1 - 7) of oxygen use and oxygen-free days.
 
• Duration (days) of mechanical ventilation
 
• Incidence of new mechanical ventilation use and duration (days) of new mechanical ventilation use.
 
• Change from baseline over time, up to Day 29, in viral load
 
• Time to negative viral titres (Day 1-29)
 
• Time to and proportion of clinical improvement. Improvement will be determined according to the WHO Clinical Progression Scale (WHO, 2020); improvement is defined as a minimum 2-
 
 |

|                                                                  |                                                                                                                                                                                                                                                                                                                                                                                                                                        |
|------------------------------------------------------------------|----------------------------------------------------------------------------------------------------------------------------------------------------------------------------------------------------------------------------------------------------------------------------------------------------------------------------------------------------------------------------------------------------------------------------------------|
|                                                                  | 
step change from randomisation in the scale up to day 29 post-randomisation
 
 
- Proportion of patients with clinical improvement (as defined above) at day 8, 15 and day 29
 
- Change at day 8 and 15 from randomisation in the WHO Clinical Progression Scale (WHO, 2020)
 
- Time to a one point change on the WHO Clinical Progression Scale at day 15 and 29
 
 |
| Translational                                             |                                                                                                                                                                                                                                                                                                                                                                                                                                        |
| Pharmacodynamics: To characterise virus and host immune response | 
 
• Change in host immune response and SARS-CoV-2 culture and sequencing (samples will be stored pending the availability of GCP-compliant assays which are currently in development)
 
• Measure immune response by aldehyde oxidase (AO) / xanthine oxidase (XO) activity
 
                                                                                                     |

## 4 TRIAL DESIGN

### 4.1 CANDIDATE SPECIFIC DESIGN

This study is a parallel group, randomised phase I trial and a parallel group, randomised, double-blind, placebo-controlled phase II trial to assess the safety, tolerability and effect of IV Favipiravir.

### 4.2 TRIAL PHASES

#### 4.2.1 Dose finding (phase I)

Phase I will be open-label assessing escalating doses of IV Favipiravir compared with Standard of Care (SoC). Patients in phase I will be recruited in cohorts of 6 (randomised to IV Favipiravir: SoC in 2:1 allocation ratio), with review of safety and tolerability between cohorts.

Dose-finding will be carried out as per the Master Protocol (Master Protocol section 4.2.1).

##### 4.2.1.1 Safety Review Committee (SRC) and dose escalation process

Refer to section 14.4 of the AGILE Master Protocol for definitions.

The SRC will review each dose cohort of 6 patients. Multiple doses of IV Favipiravir will be administered by intravenous (IV) infusion over 1 hour. Dosing regimen will be every 12 hours for 7 days duration. The starting dose will be 600 mg (BID), with a dose de-escalation possibility to a 300mg (BID) starting dose; and further dose escalations to 1200mg (BID), 1800mg (BID) and 2400mg (BID) are anticipated, with escalation and de-escalation guided by emerging safety data and decision by the SRC. Duration of monitoring will be 29 days post-first dose.

Membership of the SRC will be defined as per Study SRC charter to include the Chief Investigator ([name]) Chair of SRC, Candidate Chief Investigator, a principal investigator (PI) or delegate from the investigational site, one independent clinical member, , trial statistician and CRO trial manager or CRO

representative. At the chair's discretion, members who are unable to attend may be asked to provide comment to the chair to enable information to be shared.

The SRC will review all available safety data once the last participant recruited in the current cohort has Day 8 measures taken (where data is available beyond Day 8 for some participants, this will also be reviewed). This is inclusive of AE data, vital signs data, ECG data and clinical laboratory evaluations.

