### 1.3 SCHEDULE OF OBSERVATIONS AND PROCEDURES (Phase I and II)

|                                                       | Screening k | Day 1
(baseline) | Daily
whilst in hospital
(days 2-14) | Specific Assessments on
Days 3, 5, 8, 11 (±1 days) | Day 15
(±2 days) | Day 29
(±2 days) |
|-------------------------------------------------------|------------------------|---------------------|--------------------------------------------|-------------------------------------------------------|---------------------|---------------------|
| Informed consent                                      | X                      |                     |                                            |                                                       |                     |                     |
| Check Eligibility                                     | X a         | X                   |                                            |                                                       |                     |                     |
| Randomisation                                         |                        | X                   |                                            |                                                       |                     |                     |
| Telephone Contact b (AEs, Con-Meds)        |                        |                     | Daily apart from in hospital               |                                                       |                     |                     |
| Demographics                                          | X                      |                     |                                            |                                                       |                     |                     |
| Treatment compliance - up to day 7                    |                        |                     | X (Day 2 to 7)                             |                                                       |                     |                     |
| AE/SAE assessment                                     | X (from consent)       | X                   | X                                          | X                                                     | X                   | X                   |

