### 8.2.4 Specific Assessments on Days 3, 5, 8 and 11 ( $\pm 1$ day)

The following assessments are to be carried out on 3, 5, 8 and 11 (NB day of randomisation and start date of treatment is Day 1).

- SARS-CoV-2 surveillance NP swab
- Full blood count
- Urea and electrolytes

- Estimated GFR
- Liver Function Tests
- Uric acid
- Concomitant medication and standard of care review
- AE assessment
- Translational swab (Days 3 and 5 only)

In addition, for CST6 candidate specific trial protocol the following are required:

- Assessment using the WHO Clinical Progression Scale (WHO, 2020):
  0. Uninfected, no viral RNA detected
  1. Ambulatory mild disease, asymptomatic; viral RNA detected
  2. Ambulatory mild disease, symptomatic; independent
  3. Ambulatory mild disease, symptomatic; assistance needed
  4. Hospitalised moderate disease, no oxygen therapy (If hospitalised for isolation only, record stats as for ambulatory patient)
  5. Hospitalised moderate disease, oxygen by mask or nasal prongs
  6. Hospitalised severe disease, oxygen by NIV or high flow
  7. Hospitalised severe disease, intubation and mechanical ventilation  $pO_2/FiO_2 \geq 150$  or  $SpO_2/FiO_2 \geq 200$
  8. Hospitalised severe disease, mechanical ventilation  $pO_2/FiO_2 < 150$  ( $SpO_2/FiO_2 < 200$ ) or vasopressors
  9. Hospitalised severe disease, mechanical ventilation  $pO_2/FiO_2 < 150$  and vasopressors, dialysis, or ECMO
  10. Dead
- Non-Ventilated Patients: National Early Warning Score 2 (NEWS2) Assessment:
  - Respiration rate
  - Oxygen saturation
  - Systolic blood pressure
  - Pulse rate
  - Level of consciousness or new confusion\*
  - Temperature

\*The patient has new-onset confusion, disorientation and/or agitation, where previously their mental state was normal – this may be subtle. The patient may respond to questions coherently, but there is some confusion, disorientation and/or agitation. This would score 3 or 4 on the GCS (rather than the normal 5 for verbal response), and scores 3 on the NEWS system.
- Assessment of oxygen use (low flow, high flow, mechanical flow, mechanical ventilation use) (only if supplemental oxygen is not administered) – daily whilst in hospital
- Targeted Physical examination
- Blood (plasma and DBS) taken for PK assessments on Day 3 (pre-dose, 0-1 hr, 2-4 hr, 6-12 hr post completion of first infusion) and Day 5 (0-1hr, 6-12 hr post completion of first infusion)

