### **Day 29 ( $\pm 2$ days)**

The following assessments are to be carried out on Day 29 (+2 days) (NB day of randomisation and start date of treatment is Day 1).

- SARS-CoV-2 surveillance NP swab
- Assessment using the WHO Clinical Progression Scale (WHO, 2020):
  0. Uninfected, no viral RNA detected
  1. Ambulatory mild disease, asymptomatic; viral RNA detected
  2. Ambulatory mild disease, symptomatic; independent
  3. Ambulatory mild disease, symptomatic; assistance needed
  4. Hospitalised moderate disease, no oxygen therapy (If hospitalised for isolation only, record stats as for ambulatory patient)
  5. Hospitalised moderate disease, oxygen by mask or nasal prongs
  6. Hospitalised severe disease, oxygen by NIV or high flow
  7. Hospitalised severe disease, intubation and mechanical ventilation  $pO_2/FiO_2 \geq 150$  or  $SpO_2/FiO_2 \geq 200$
  8. Hospitalised severe disease, mechanical ventilation  $pO_2/FiO_2 < 150$  ( $SpO_2/FiO_2 < 200$ ) or vasopressors
  9. Hospitalised severe disease, mechanical ventilation  $pO_2/FiO_2 < 150$  and vasopressors, dialysis, or ECMO
  10. Dead
- Non-Ventilated Patients: National Early Warning Score 2 (NEWS2) Assessment:
  - Respiration rate
  - Oxygen saturation
  - Systolic blood pressure
  - Pulse rate
  - Level of consciousness or new confusion\*
  - Temperature

\*The patient has new-onset confusion, disorientation and/or agitation, where previously their mental state was normal – this may be subtle. The patient may respond to questions coherently, but there is some confusion, disorientation and/or agitation. This would score 3 or 4 on the GCS (rather than the normal 5 for verbal response), and scores 3 on the NEWS system.
- Full blood count
- Urea and electrolytes
- Estimated GFR
- Liver Function Tests
- Uric acid
- Concomitant medication and standard of care review
- AE assessment
- Targeted physical exam
- Urine pregnancy test for WOCBP
- Urinalysis

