### 9.2 REPORTING WINDOWS

All AEs will be collected up to Day 29 post-dose. SAEs will be collected from dose administration through to Day 29 follow-up visit. However, any SAEs assessed as related to study participation (e.g., study intervention, protocol-mandated procedure, invasive tests or change in existing therapy) will be recorded from the time participant consents to participate in the study.

Each time there is a change in grade of an adverse event this should be recorded on a separate log line on the adverse event form on the eCRF. Refer to the eCRF Guidance on how to report this on Rave. The investigator should notify the trial sponsor of any death or adverse event occurring at any time after a patient has discontinued or terminated trial participation that may reasonably be related to this trial.

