##### Decision Making

Dose escalation will be based on review of safety data up to Day 8 on the safety population. Doses are deemed to be safe if the risk of dose-limiting toxicity (DLT) being at least 30% larger in IV Favipiravir than standard of care is less than 25%. Dose de-escalation for the starting dose will be reviewed by the SRC and guided by their decision depending on DLTs.

A two parameter Bayesian dose escalation model will be used to recommend the next cohort dose or the recommended phase II dose. The model will target a safe dose with an additional DLT risk of 20% (the target interval of 15-25%) above standard of care.

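### The ±1-day window lets the Day 8 visit that opens the dose-escalation review fall on Day 7, before the DLT period closes and usually before a full course ends; separately, the Day 29 window is stated in two ways

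*Protocol*

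**What the plan says.** **Day 8.** The primary Phase I endpoint counts DLTs up to Day 8 (synopsis and section 3.1). Section 10.3.1 uses the same horizon for the decision: "Dose escalation will be based on review of safety data up to Day 8 on the safety population". Section 4.2.1.1 sets the point at which the committee meets: "The SRC will review all available safety data once the last participant recruited in the current cohort has Day 8 measures taken". It includes laboratory evaluations in the material reviewed, and adds that data beyond Day 8 are considered where some participants have them.

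The column heading in schedule 1.3 reads "Days 3, 5, 8, 11 (±1 days"), and the heading of section 8.2.4 has the same window. Section 8.2.4 defines the day count: "NB day of randomisation and start date of treatment is Day 1". On dosing, section 4.2.1.1 says: "Dosing regimen will be every 12 hours for 7 days duration". Sections 6.1 and 8.2 add that treatment is given only while the patient is in hospital, so a course can be shorter.

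Between visits, section 8.2.3 and the schedule provide for adverse events to be documented daily from Day 2 to Day 14, in hospital or by telephone. Bloods on those days follow standard of care.

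**Day 29.** The schedule and the section heading allow ±2 days. The sentence below the heading reads: "The following assessments are to be carried out on Day 29 (+2 days"). Section 9.2 collects adverse events up to Day 29, but for serious events it says: "SAEs will be collected from dose administration through to Day 29 follow-up visit". The schedule marks this visit as end of study.

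**The concern.** The escalation review opens on a visit that has a window, not on completion of the period whose data it is meant to assess. If the last participant's Day 8 visit is made on Day 7, the visit complies and the stated trigger is met. The DLT period is then still open and, for a patient on a full course, infusions are usually still to come.

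Two things are at stake. First, a decision that may as much as double the dose (section 4.3) can be taken up on data that stop short of the Day 8 basis in section 10.3.1. Second, laboratory toxicity after the final infusions may have no protocol-mandated blood test inside the DLT period. The protocol itself reports that favipiravir accumulates in plasma on repeat dosing and raises uric acid (sections 2.2 and 4.3), so laboratory data late in the course are relevant. Each cohort has only 4 patients on active drug.

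The Day 29 point is a separate one. It concerns the end of serious-event collection and the Day 29 mortality and time-to-death endpoints, and it has no part in escalation.

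**Working it through.** The protocol prints no figure to reproduce here. The check is a day count.

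**Inputs from the protocol.** Day 1 is the day of first treatment. Infusions are 12 hours apart for 7 days and last 1 hour. The visit window is 8 ± 1, so Day 7 to Day 9. The DLT period is taken to run to the end of Day 8.

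**Assumptions.** Clock times are not given. The first infusion at hour *f* of Day 1 is ranged over 00:00 to 23:00, and the visit is tried at 09:00, 13:00 and 17:00. Spacing is nominal.

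**Course length.** 7 × 24 / 12 = 14 infusions. Infusion *k* starts at *f* + 12(*k* − 1) hours from the start of Day 1, so the 14th starts at *f* + 156 and ends at *f* + 157. With *f* = 8 it starts at 20:00 on Day 7; with *f* = 20, at 08:00 on Day 8.

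**Infusions completed at a Day 7 visit** (visit time *t* = 144 + clock hour; infusion *k* counts if *f* + 12(*k* − 1) + 1 ≤ *t*):

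| First infusion, Day 1 | 09:00 | 13:00 | 17:00 |
|---|---|---|---|
| 06:00 or 08:00 | 13 | 13 | 13 |
| 10:00 or 12:00 | 12 | 13 | 13 |
| 14:00 or 16:00 | 12 | 12 | 13 |
| 18:00 or 20:00 | 12 | 12 | 12 |
| 22:00 or 23:00 | 11 | 12 | 12 |

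So 1 to 3 infusions are outstanding: 1/14 = 7% to 3/14 = 21% of a full course. All 14 are complete on Day 7 only if *f* + 157 ≤ *t*. For a 17:00 visit (*t* = 161) this needs a first infusion by 04:00 on Day 1. With a first infusion at 08:00 it needs a visit at 21:00 or later (157 + 8 = 165 = 144 + 21).

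**DLT period still to run.** From 09:00 on Day 7 to the end of Day 8 is 15 + 24 = 39 hours. For a first infusion at 08:00 the period is 192 − 8 = 184 hours, and 39/184 = 21%. For 20:00 it is 192 − 20 = 172 hours, and 39/172 = 23%.

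**Next mandated bloods.** 11 ± 1 gives Day 10 to Day 12, all after Day 8. A Day 7 draw is then the last mandated set inside the DLT period.

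**With a 0/+1 window.** At 09:00 on Day 8, *t* = 177, so all 14 are complete if *f* ≤ 20. A first infusion after 20:00 leaves 13 of 14 complete at that hour. By 13:00 on Day 8 (*t* = 181) all 14 are complete for every start time.

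**Day 29.** ±2 gives Day 27 to Day 31; +2 gives Day 29 to Day 31. Only the first allows an early close, of up to 2 days.

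**The case against.** The strongest reply is that section 10.3.1 already fixes the decision basis as data up to Day 8, and that section 4.2.1.1 gives only the earliest moment for the review. A visit window moves procedures; it does not shorten the DLT period. This stands as far as it goes. A reader might infer that the protocol cuts the DLT period to Day 7, and it does not. But nothing in the text makes the trigger wait for the period that section 10.3.1 names, so the two sections still need to be reconciled.

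A second reply is that safety follow-up continues. Adverse events are documented daily to Day 14. A patient with infusions outstanding is by definition an in-patient, for whom the schedule marks daily vital signs and examination, although section 8.2.3 lists both under standard of care and clinical indication. Section 8.3 allows extra laboratory tests where appropriate. This also stands. It rules out the tempting reading that one early visit removes a whole patient, a quarter of the 4 on active drug, from the decision. It does not supply a mandated blood test after the final infusions.

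Third, outstanding infusions are not an issue for standard-of-care patients (2 of 6 per cohort) or for those discharged before Day 7.

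Fourth, the master protocol, the SRC charter and the time-windows working instruction are not shown and could contain a rule. This protocol cites the working instruction only for Day 1 vital signs and dosing times.

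On Day 29, the objection that adverse-event collection is tied to Day 29 and not to the visit is correct. Only serious events are tied to the visit.

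**Conclusion.** The point holds in a limited form. A compliant Day 7 visit by the last participant meets the stated trigger before the DLT period has closed. On a full course and at ordinary daytime hours, 1 to 3 of 14 infusions are still to come, and a 09:00 visit leaves about 21–23% of the DLT period. These figures rest on the assumed clock times and nominal 12-hour spacing. The firm consequences are an early opening of the review and, for any active patient on a full course seen on Day 7, probably no mandated blood test between the final infusions and the end of the DLT period.

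The Day 29 window is a plain contradiction within the protocol. Under ±2, a Day 27 visit closes serious-event collection as section 9.2 defines it, and is the last scheduled contact before Day 29 mortality is due. A reader might infer that all adverse-event collection then stops, or that Day 29 mortality must go unobserved. The text supports neither: adverse events are collected to Day 29, section 4.2.1.1 sets monitoring at 29 days after first dose, and section 8.2 allows patient status to be obtained by telephone. What is missing is a scheduled contact that secures it.

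**What to change.** 1. In schedule 1.3 and section 8.2.4, give the Day 8 assessments a one-sided window (0/+1 day), so that the scheduled bloods and examination fall at or after the end of the course. For a first infusion after 20:00 on Day 1, an early-morning Day 8 assessment would still precede the last infusion, so a later hour that day is needed.
2. Reconcile the review trigger in section 4.2.1.1 with the data basis in section 10.3.1, so that both refer to the same completed period.
3. Reconcile the Day 29 window across schedule 1.3, the Day 29 section and section 9.2, so that serious-event and mortality follow-up reaches Day 29 for every patient.
4. Check the master protocol, the SRC charter and the time-windows working instruction for an existing rule, and cite it if there is one.

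The cost is a wording amendment and an escalation review that may start up to about one day later per cohort. The schedule serves both phases, so the narrower Day 8 window would also apply in Phase II unless limited to Phase I. The change concerns when assessments are made; no dose or treatment rule is proposed.
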